### Measures

#### The Proportion of Studies Completed

The primary outcome of interest is the proportion of studies completed. A study is considered complete if a participant reaches the end of a trial without a study failure (involuntary withdrawal) or voluntary withdrawal. A study failure occurs when there is insufficient data generated during baseline or any treatment period due to missed treatments (self-reported) or incomplete assessments. Participants must complete all assigned treatment and assessment tasks for 1/3 of the days in each period to avoid study failure and involuntary withdrawal, except for the 5-day study where all tasks must be completed each day because there is only one day per period. For the 15-day and 27-day trials, we inevitably expect participants to miss some tasks during these periods, so we wanted to allow for some nonadherence. While the requirement of task completion for 1/3 of the days in each treatment period is somewhat arbitrary, the choice of 1/3 of the days means that, at a minimum, completed 15-day trials will at least have the same amount of data as completed 5-day trials and are also likely to have more. We applied the same criteria to the 27-day trial so that the criteria for study failure are uniform across all three study durations. It is also worth noting that the 3 study lengths are primarily dictated by our randomized, counterbalanced, crossover design that defines N-of-1 trials: NABBA or NBAAB, where N is baseline, A is treatment period A, B is treatment period B, and AB or BA is a block. The minimum N-of-1 trial for a counterbalanced design with two blocks is five days if you have only one day per treatment period and one day of baseline.

We anticipate that a 27-day trial approaches what is likely to be the maximum number of days we could expect people to participate with reasonable adherence for this study, which requires daily tasks. The 15-day trial splits the difference between these two extremes. Put another way, we chose to vary treatment period lengths by one day for the 5-day trial, three days for the 15-day trial, and five days for the 27-day trial. We could have selected a different design, such as treatment periods that are 1, 2 and 3 days long rather than 1, 3 and 5 days long for each group; however, to evaluate the impact of study durations and notification levels on completion rates, we reasoned it would be better to have a more extensive spread across the three groups.

#### Adherence

Treatment adherence is recorded as true for days when a participant completes a cognitive assessment and does not report treatment nonadherence. A participant is instructed to report any treatment nonadherence (eg, a missed treatment or the use of caffeine on a baseline day) in the app during the trial. At the end of the trial, participants are prompted to review a summary of their treatment adherence and may, if necessary, record missed treatments at this time as well. Assessment adherence is recorded as true when a participant completes all three cognitive tests in a daily cognitive assessment according to the user-specified schedule. Otherwise, assessment nonadherence is recorded (for both incomplete assessments and assessments that were not started). Daily adherence is recorded as true when a participant achieves both treatment adherence and assessment adherence for a given day during the trial.

We will also measure trial adherence, which is defined as the proportion of total actions completed by a participant during a trial. Here total actions are defined as the number of requested treatment actions (to take a treatment or abstain from all treatments) plus the number of requested assessment actions (take a cognitive assessment) during a trial. During the baseline period, participants take two actions per day in the form of abstaining from treatments and completing one cognitive assessment. During a treatment period, participants take two actions per day in the form of taking one treatment plus completing one cognitive assessment. The total number of actions requested, and the minimum number of actions required for each study duration are outlined in Table 2.

**Table 2 table2:** Total number of actions requested, and the minimum number of actions required for each study duration.

Study duration	Total number of actions requested	Minimum number of actions required to avoid study failure
5-day study	10	10
15-day study	30	10
27-day study	54	22

#### Motivation and Notification Levels

Before the trial begins, we will ask participants to self-report their motivation level to learn their results on a 5-point ordinal scale (see Multimedia Appendix 2). Also, participants will be randomized into two notification levels (light or moderate). However, since Apple does not allow iOS apps submitted to the App Store to require that users allow app notifications, we will also record the number of participants that turn off notifications. We anticipate that the number of individuals that turn off notifications will be rare, in part due to a warning message we included as a modal in the app that discourages this behavior, due to the likelihood of failure to complete study tasks according to the user-specified daily schedule (see Multimedia Appendix 1).

#### Proportion of Trials That Yield Statistically Meaningful Results

For each study duration, we will also measure the proportion of completed N-of-1 trials that yield statistically meaningful results as determined by the N1 app, for the comparisons: (1) caffeine versus baseline; and (2) caffeine plus L-theanine versus baseline. As described elsewhere, the N1 app considers a trial to have yielded a statistically meaningful result if the coefficient of treatment effect is significantly different from zero at the 80% confidence level in at least one of the three cognitive tests (eg, if taking caffeine relative to baseline, with or without L-theanine, produces an effect on cognitive performance measured by at least one of the three cognitive tests) [6]. The 80% confidence level is arbitrary, and we anticipate future versions of the N1 app will allow individuals to select the confidence level they seek.

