## Introduction

### Background

The purpose of this study is to evaluate factors that may impact study completion and adherence in the context of app-based N-of-1 trials. A common challenge for digital research studies is the poor engagement of users [1]. The “law of attrition,” as Eysenbach described it in 2005, is of special concern to app-based N-of-1 studies. Unlike a conventional, two-arm, randomized controlled trial (RCT) where a minimum sample size is calculated to detect a treatment effect that also takes into account an expected rate of attrition across the enrolled population, N-of-1 trials operate at the level of the individual, and there is 1 participant per trial. Typically, in an N-of-1 trial, an individual alternates between treatments (ie, “multiple crossover”), and outcomes are measured during each treatment period [2,3]. If there is attrition and the participant fails to complete an N-of-1 trial, there is no result for that individual.

Moreover, if a participant completes an N-of-1 trial, the result may still fail to achieve a level of statistical meaningfulness, especially for shorter trial durations. In this way, any person that aims to design an N-of-1 trial that is capable of informing decision-making for treatment selection for a single individual must strike the right balance between the ease of trial completion and the generation of meaningful results. Therefore, we aim to collect evidence about critical factors that may impact rates of study completion in the context of app-based N-of-1 trials. We hope these findings will inform the design of future app-based N-of-1 trials and improve the adoption of N-of-1 methods and tools.

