### Hypotheses

The primary hypothesis is that shorter trials will have higher rates of completion compared to longer trials. The null hypothesis is that no correlation exists between study completion and study duration. We also hypothesize that higher rates of study completion will be achieved with more frequent reminders to complete study tasks, in the form of app-based notifications, especially since the Brain Boost Study requires participants to complete tasks during a specific window of time each day during the trial. The null hypothesis is that no correlation exists between study completion and notification level.

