### Power and Sample Size

The study will be sufficiently powered (>80%; alpha=0.05) if 640 individuals begin the study, are randomized into 3 study lengths (5, 15, or 27 days) according to a randomization percent allocation of 20%, 60%, 20%, and achieve rates of completion of 30%, 20%, and 10%, respectively (see Table 3).

**Table 3 table3:** The minimum number of participants we aim to enroll in each study duration.

Study duration	Randomization allocation (%)	Participants who begin study (n)	Estimate of completion rate (%)	Participants who complete study (n)
5-day study	20	128	30	38
15-day study	60	384	20	77
27-day study	20	128	10	13
Total	100	640	60	128

For the sample size estimate, the Hsieh sample size correction for multiple logistic regression was used, which assumes correlation among covariates and therefore adjusts the sample size accordingly [9]. We estimated this correlation to be equal to 0.25. With these assumptions, 97 completed studies are required to discern whether the study length and notification level are associated with the rates of study completion. To estimate how precise we may be, we used sample size tables for each predictor (see Multimedia Appendix 4).

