#### Exploratory Analyses

We will also use descriptive statistics to summarize measures collected in the Brain Boost Study. We will compare the proportion of studies completed and trial adherence across the six groups of participants (three study durations and two notification levels), removing from this analysis anyone that turned off notifications. We will also compare the proportion of completed trials that are deemed by the N1 app to demonstrate a meaningful difference in treatment response on any of the cognitive tests, across the three study durations.

We also want to learn about the factors that influence the measure of trial adherence to improve future study designs. We will use Bayesian methods for exploratory analysis to get a baseline for future analyses, which we expect will also use Bayesian methods of analysis. The exploratory analysis will utilize a Bayesian survival-style model with semicompeting risks throughout the study. It will be assumed that a participant is in the study up until the time of study completion, voluntary withdrawal, or involuntary withdrawal (ie, study failure). Daily adherence will be assessed among all participants in the study on a given study day. There will be two types of events considered: (1) daily nonadherence, as a nonterminal repeating event; and (2) early withdrawal (including both voluntary withdrawal and involuntary withdrawal due to study failure) as a terminal (nonrepeating) event. The daily rate of nonadherence and early withdrawal will be modeled as a Poisson process with the rates impacted by several covariates, including study day (number of days since the start of the study, estimated with a random walk prior), notification level (light versus moderate); self-reported motivation level (5-point ordinal scale), day of the week (if distinguishable from study day), and subject-specific shared frailty term.

The cumulative probability of early withdrawal can be used to estimate the inverse probability of study completion. Also, the daily rates of adherence can be used to improve study design for future participants, depending on self-reported motivation and subject-specific characteristics. As in the primary analysis of the study completion rate, we will additionally adjust this analysis of adherence for age and sex.

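### The exploratory comparison of meaningful results across durations is restricted to completers, so it is not a randomised comparison and cannot by itself address the balance between finishing and getting a result

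*Protocol article*

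**What the plan says.** The Measures section on statistically meaningful results defines the quantity, for each duration, as "the proportion of completed N-of-1 trials that yield statistically meaningful results". The Exploratory Analyses section repeats that denominator: "We will also compare the proportion of completed trials that are deemed by the N1 app to demonstrate a meaningful difference in treatment response". The groups compared are the three durations. A trial counts as meaningful if at least one of three cognitive tests shows a treatment coefficient different from zero at the 80% confidence level.

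Completion is the primary outcome. The Hypotheses section states: "The primary hypothesis is that shorter trials will have higher rates of completion compared to longer trials". The Power and Sample Size section plans for arms that "achieve rates of completion of 30%, 20%, and 10%, respectively". The section on the proportion of studies completed requires every task on every day in the 5-day arm, but only one third of the days in each period in the longer arms. Table 2 gives the minimum as 10 of 10 actions, 10 of 30 and 22 of 54.

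The Background says that a participant who does not complete has no result, and that a designer of such trials "must strike the right balance between the ease of trial completion and the generation of meaningful results". The Randomization section uses the same trade-off to justify the 20/60/20 allocation. The article describes no analysis of meaningful results with randomised participants or beginners as the denominator.

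**The concern.** Completers in the three arms are subsets chosen by an event that follows randomisation. The plan expects that event to differ threefold between the 5-day and 27-day arms, and it is defined by different rules. A difference in the completers' share therefore mixes two things: the effect of collecting more data, and differences in who is left.

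The completers' share also leaves out those who never reach a result. A long trial can show the highest share among finishers while giving a result to fewer of the people who started it. Anyone using this comparison to weigh short against long trials would see only one half of the balance that the Background describes. The plan reports the two halves separately and never compares their product between the randomised groups.

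**Working it through.** **Inputs.** Number of beginners ("if 640 individuals begin the study"), allocation 20/60/20 and completion rates 30/20/10%, all from Power and Sample Size. The article gives no expected share of meaningful results among completers. Write these shares as q5, q15 and q27; any value below is an assumption.

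**Step 1: reproduce Table 3.** Completers = 640 × allocation × completion rate.
- 5 days: 640 × 0.20 × 0.30 = 38.4 (Table 3: 38)
- 15 days: 640 × 0.60 × 0.20 = 76.8 (Table 3: 77)
- 27 days: 640 × 0.20 × 0.10 = 12.8 (Table 3: 13)
- Total: 128.0 (Table 3: 128)

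**Step 2: yield per beginner.** Yield = completion rate × q, that is 0.30 × q5, 0.20 × q15 and 0.10 × q27.
- 27 days above 5 days needs q27 > (0.30/0.10) × q5 = 3 × q5.
- 27 days above 15 days needs q27 > (0.20/0.10) × q15 = 2 × q15.
- 15 days above 5 days needs q15 > (0.30/0.20) × q5 = 1.5 × q5.
- The 27-day yield cannot exceed 10%. It cannot beat 5 days once q5 reaches 1/3, nor 15 days once q15 reaches 1/2.

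**Step 3: illustrations (assumed shares).**

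| q5 / q15 / q27 among completers | Yield per beginner (5 / 15 / 27 days) | Effect on order |
|---|---|---|
| 50 / 65 / 80% | 15.0 / 13.0 / 8.0% | fully reversed |
| 25 / 45 / 65% | 7.5 / 9.0 / 6.5% | 27 days moves from first to last |
| 20 / 40 / 70% | 6.0 / 8.0 / 7.0% | 15 days first instead of 27 |

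For the two extreme arms alone, q5 = 50% and q27 = 90% give 0.30 × 0.50 = 15% and 0.10 × 0.90 = 9%.

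**Step 4: sensitivity to the completion rates.** With flatter completion of 30/25/20% and shares of 50/65/80%, the yields are 15.0, 16.3 and 16.0%, so 15 days is first instead of 27. With equal completion in all arms the order does not change.

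**Step 5: the criterion for a meaningful result.** Assume no true effect, independent tests and nominal error rates. The chance that at least one of three tests passes at 80% confidence is 1 − 0.8³ = 48.8% for one comparison. If either of the two comparisons with baseline counts (six independent tests), it is 1 − 0.8⁶ = 73.8%. If the three tests were perfectly correlated, it would be 20%. At q5 = 48.8%, the 5-day yield is 0.30 × 0.488 = 14.6% with no true effect at all, above the 10% ceiling for 27 days. At q5 = 20%, q27 would have to exceed 60%.

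**Step 6: precision.** With 13 completers and q27 = 65%, the 95% half-width is 1.96 × √(0.65 × 0.35/13) = 26 percentage points. Per beginner, for 15% versus 8% with 128 in each arm, the half-width of the difference is 1.96 × √((0.15 × 0.85 + 0.08 × 0.92)/128) = 7.8 points around a difference of 7.0.

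**The case against.** The strongest reply is that the completers' share answers a proper question. The Background asks two things in turn: whether a participant finishes and, given that, whether the result is meaningful. The share among completers answers the second. The analysis is labelled exploratory, and its section opens with descriptive statistics. Completion by duration is the headline result, so a reader can multiply the two figures. All of this stands. It limits the weight of the point, but it does not make the completers' comparison a randomised one, and no interval for the product is planned.

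Four stronger readings might be inferred, and the documents do not support them:
- *That the plan will pick the wrong duration.* No objective, hypothesis or decision rule selects a best duration. The stated purpose is to study factors affecting completion. The trade-off appears as motivation and as the reason for the allocation.
- *That duration is known to drive completion.* This is the hypothesis under test, and the rates are planning values that the article itself calls hard to estimate.
- *That 27-day completers are the more adherent group.* By rule, 5-day completers are fully adherent while 27-day completers may finish with 22 of 54 actions. The direction of selection is not established.
- *That yield per participant is the better ranking and should replace the completers' share.* Under the any-of-three rule it could place short trials first on chance findings alone (Step 5). It belongs beside the completers' share.

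**Conclusion.** The point holds as a moderate one. The completers-only denominator is fixed in two places, so this is a stated choice and not a detail left to a fuller document. As a description of finishers it is sound. As a comparison between durations it lacks the protection of randomisation, and read alone it cannot address the balance set out in the Background and Randomization sections.

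At the planning rates, a first place for 27 days among completers carries over to beginners only if its share is more than 3 times the 5-day share and more than 2 times the 15-day share. This rests on completion rates of 30/20/10% and on assumed shares, since the article gives none. The gap between the two orders narrows as completion becomes more equal and vanishes when it is equal. The primary analysis is unaffected.

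**What to change.** In the Measures section on statistically meaningful results and in Exploratory Analyses:

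1. Add the proportion of all participants randomised to each duration who both complete and obtain a meaningful result, counting non-completers as no result. Compare it across the three durations with confidence intervals.
2. Give the same proportion among all who begin as a secondary figure. It should come second because beginning requires at least one fully adherent baseline day, and the baseline differs by arm: 5 − 4 × 1 = 1 day, 15 − 4 × 3 = 3 days and 27 − 4 × 5 = 7 days. Beginning is therefore itself observed after assignment.
3. Keep the completers' share as a descriptive figure, and say that it describes those who finish and is not a randomised comparison.
4. State that the 80%-confidence, any-of-three rule carries a high chance of a false meaningful result, and that this affects both measures.
5. State the denominator in the abstract, which refers only to trials.

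The cost is a few sentences and one further tabulation. Assignment, completion or withdrawal, and the app's verdict on each completed trial are already part of the planned data, so nothing new is collected and the sample size does not change. With about 128 beginners in each of the two smaller arms, the intervals will be wide (Step 6), and the comparison should remain exploratory.

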#### Exit Survey

We will also invite enrolled participants to provide feedback about the N1 app and the Brain Boost Study through an optional exit survey administered at the time of study completion, during voluntary withdrawal, or at study failure via an automated email with a link. The anonymous survey will not be linked with individual user accounts. The exit survey includes a modified version of the 2-item Usability Metric for User Experience (UMUX-Lite) and up to 15 optional questions related to the participant experience with the app and the study (see Multimedia Appendix 3) [7]. The survey will be conducted in a browser outside of the N1 app.

#### Bug Reports and App Crashes

We will record the number of software bug reports submitted anonymously by users through a third-party tool linked from inside the N1 app. We will also record the number of app crashes recorded from those users who have opted-in to share their diagnostics and app usage information with app developers in App Store Connect, an administrative platform for managing and monitoring iOS apps submitted to the Apple App Store [8].

#### Other Collected Data

We collect sex (male, female, other) and year of birth (YYYY). For each participant in a trial, we will also timestamp planned and completed actions, and record the following dates: planned trial start and end dates, dates of adherence and nonadherence (treatment and assessment adherence), and dates of early withdrawal or completion.

### Power and Sample Size

The study will be sufficiently powered (>80%; alpha=0.05) if 640 individuals begin the study, are randomized into 3 study lengths (5, 15, or 27 days) according to a randomization percent allocation of 20%, 60%, 20%, and achieve rates of completion of 30%, 20%, and 10%, respectively (see Table 3).

**Table 3 table3:** The minimum number of participants we aim to enroll in each study duration.

Study duration	Randomization allocation (%)	Participants who begin study (n)	Estimate of completion rate (%)	Participants who complete study (n)
5-day study	20	128	30	38
15-day study	60	384	20	77
27-day study	20	128	10	13
Total	100	640	60	128

For the sample size estimate, the Hsieh sample size correction for multiple logistic regression was used, which assumes correlation among covariates and therefore adjusts the sample size accordingly [9]. We estimated this correlation to be equal to 0.25. With these assumptions, 97 completed studies are required to discern whether the study length and notification level are associated with the rates of study completion. To estimate how precise we may be, we used sample size tables for each predictor (see Multimedia Appendix 4).

### Data Analysis Plan

#### Primary Analysis

All study data, unless otherwise noted, will be collected through the N1 app, and stored in Health Insurance Portability and Accountability Act (HIPAA)-compliant cloud storage. Statistical analyses will be conducted primarily using R version 3.6 (The R Foundation, Vienna, Austria). We will use a multiple logistic regression model to discern the relationship between study duration and notification level with the proportion of studies completed among participants who begin a study. Participants who begin a study are defined as those who achieve both treatment adherence and assessment adherence for at least one day during the baseline period. Participants that do not begin the study will be removed from the analysis. We will adjust these results for any variance in completion rate by age and sex.

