### Study Design

This study aims to evaluate a novel platform for conducting single-patient, multiple crossover studies (N-of-1 trials). For purposes of clarity, this protocol describes our methods to assess factors associated with study completion, along with several exploratory measures and analyses. The study design, interventions, cognitive assessment instruments, and methods for evaluating whether there is a detectable treatment effect for an individual participant enrolled in the Brain Boost Study based on their performance on the cognitive assessments are described elsewhere [6]. Participants enrolled in the Brain Boost Study follow a treatment schedule, guided by a mobile app (N1 app), where they alternate between the two treatments: caffeine (treatment A) or caffeine combined with L-theanine (treatment B) during a prespecified window of time. Participants are also asked to complete an app-based cognitive assessment during a prespecified window of time each day. The daily cognitive assessment includes three separate cognitive tests: the Stroop Test, the Remote Associates Test, and the Trailmaking Test [6]. They complete their tasks during one baseline period (where no treatment is assigned), and during four treatment periods where either treatment A or treatment B is assigned according to counterbalanced block design. Participants are not compensated, and the app is free to use. Only after a trial is completed does a participant see their results from the cognitive assessments.

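### The primary analysis keeps only participants with an adherent baseline day, but assigned duration sets whether they have 1, 3 or 7 days in which to achieve one

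*Protocol article*

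**What the plan says.** The Primary Analysis section models "the proportion of studies completed among participants who begin a study". It defines beginners as "those who achieve both treatment adherence and assessment adherence for at least one day during the baseline period" and then states: "Participants that do not begin the study will be removed from the analysis". The exploratory analyses add no analysis of everyone randomised.

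Study Design gives each trial "one baseline period (where no treatment is assigned), and during four treatment periods". The section on the proportion of studies completed sets treatment-period lengths at "one day for the 5-day trial, three days for the 15-day trial, and five days for the 27-day trial", and says the minimum design is "five days if you have only one day per treatment period and one day of baseline". The same section makes insufficient data in the baseline period a study failure. The threshold is all tasks on one third of the days in each period, or every day in the 5-day study.

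The primary hypothesis is that "shorter trials will have higher rates of completion compared to longer trials". Power and Sample Size counts its 640 among beginners and describes the sequence as "if 640 individuals begin the study, are randomized into 3 study lengths (5, 15, or 27 days".

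**The concern.** Assigned duration fixes the length of baseline, so whether someone begins is decided after assignment and under different conditions in each arm. A 5-day participant has one chance. A 27-day participant has seven and may miss six of them.

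The exclusion also cuts across the outcome definition. A 5-day participant who misses the only baseline day is a study failure under that definition, yet leaves the denominator.

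At stake is whether the primary duration comparison is still one between randomised groups. Removing early failures from the shorter arms more than from the longest one can produce a duration effect where none exists, or enlarge a real one.

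**Working it through.** **1. Baseline length.** Baseline days = duration − 4 × treatment-period days:

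- 5-day: 5 − 4×1 = 1
- 15-day: 15 − 4×3 = 3
- 27-day: 27 − 4×5 = 7

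**2. Reproducing Table 2.** With two actions a day and a one-third rule in each period, minimum actions = 2 × [4 × ceil(t/3) + ceil(baseline/3)], where t is the treatment-period length.

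- 5-day: 2 × (4×1 + 1) = 10
- 15-day: 2 × (4×1 + 1) = 10
- 27-day: 2 × (4×2 + 3) = 22

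These match Table 2 exactly (10, 10, 22), so the 7-day baseline is confirmed.

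**3. Who is removed.**

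| Arm | Days needed to pass baseline | Days needed to begin | Task-based baseline failures left in the analysis |
|---|---|---|---|
| 5-day | 1 of 1 | 1 of 1 | none |
| 15-day | 1 of 3 | 1 of 3 | none |
| 27-day | 3 of 7 | 1 of 7 | those with 1–2 adherent days |

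**4. Effect on the rates.** Every completer has begun, so the exclusion removes only non-completers: rate among beginners = P(complete) / P(begin). If each baseline day is independently adherent with probability q, P(begin) = 1 − (1 − q)^k for k = 1, 3, 7. The article gives no value for q; 0.5 to 0.9 is an assumed range.

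**5. No true duration effect.** Let completion among all randomised be c in every arm, with 640 beginners arising from 20/60/20 allocation. The overall two-degree-of-freedom test has noncentrality λ = Σ nᵢ(pᵢ − p̄)² / [p̄(1 − p̄)].

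Worked case, q=0.7 and c=20%:

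- P(begin) is 0.70, 0.973 and 1.00.
- The rates among beginners are 0.20/0.70 = 28.6%, 0.20/0.973 = 20.6% and 20.0%.
- About 693 are randomised, and the beginners number about 97, 404 and 139.
- λ = 3.25, so the nominal 5% test rejects 35% of the time.

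| q | P(begin), 5/15/27 days | Rates among beginners, c=10% | Odds ratio 5 v 27 days, c=10% | Rejection, c=10% | Rejection, c=20% |
|---|---|---|---|---|---|
| 0.9 | 0.90/0.999/1.00 | 11.1/10.0/10.0% | 1.12 | 6% | 7% |
| 0.8 | 0.80/0.992/1.00 | 12.5/10.1/10.0% | 1.29 | 9.5% | 16% |
| 0.7 | 0.70/0.973/1.00 | 14.3/10.3/10.0% | 1.50 | 17% | 35% |
| 0.5 | 0.50/0.875/0.992 | 20.0/11.4/10.1% | 2.23 | 53% | 89% |

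**6. If adherence is a property of the person.** Suppose 20–40% never start and the rest adhere on 85–95% of days. The same calculation then rejects about 5–17% of the time. For example, with 30% never-starters and 90% adherence otherwise, day-1 adherence is 0.7 × 0.9 = 63%, and rejection is 6.5% (c=10%) to 8.6% (c=20%).

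**7. Power, before and after.** Under Table 3, 38.4 + 76.8 + 12.8 = 128 completers of 640, so p̄ = 0.20. Then λ = (128×0.01 + 128×0.01)/0.16 = 16, and power for the overall duration test is 95.7%. The claim of more than 80% therefore reproduces, and it still does (88.3%) if the Hsieh correction is taken as multiplying the sample size by 0.75.

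Now suppose 30/20/10% hold among beginners, non-beginners count as not completed, and enough are randomised to yield 640 beginners:

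- q=0.9: rates 27.0/20.0/10.0%, λ = 12.3, power about 89% before the Hsieh correction
- q=0.7: rates 21.0/19.5/10.0%, λ = 7.5, power about 69% before the Hsieh correction

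**The case against.** Four arguments favour the plan.

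- **The restriction is open and prespecified.** The Objective targets people who begin, and completion among starters is a reasonable quantity to want. This stands as an answer to any suggestion of concealment. It does not restore comparability, because the same word selects different populations in the three arms.

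- **The bias may be small.** This stands. At q=0.9 the test is close to its nominal level. Independence between days is also doubtful: the Discussion describes fast attrition and entrants who may be more curious than committed. A reader might infer from the lower values of q that the primary test has a grossly inflated false-positive rate. The documents do not support that, since they give no baseline adherence figure and person-driven non-starting brings rejection down to about 5–17%.

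- **The direction is not guaranteed.** This also stands. The Discussion says abstaining from caffeine through baseline may be hard, and a 27-day assignee faces seven such days. If that assignment multiplied P(begin) by less than about 0.90 (q=0.9), 0.70 (q=0.7) or 0.50 (q=0.5), the 5 v 27-day bias would reverse. Whether participants see their duration before baseline cannot be read from the available text. A reversal would still leave an arm-dependent selection. Nor is this a statement of net bias: the every-day rule in the 5-day arm works against that arm.

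- **The wording of Power and Sample Size puts beginning before randomisation.** Taken literally, that would remove the problem. It does not fit a baseline whose length depends on the assigned duration.

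Two further inferences go too far. Baseline length does not differ by notification level, so any distortion there comes only from reminders affecting baseline adherence, and neither its size nor its direction is known. The 128/384/128 split in Table 3 is a planning target. Beginners would depart from it noticeably at q=0.7 (97/404/139) but little at q=0.9 (118/392/131).

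**Conclusion.** The concern holds as a structural fault in the primary analysis set. The begin criterion is applied after assignment and means 1 of 1, 1 of 3 or 1 of 7 days. It removes all task-based baseline failures in two arms and only some in the third, contrary to the outcome definition. These points follow from the article's own figures and need no assumption.

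That the exclusion inflates the 5-day rate, and so favours the primary hypothesis, is conditional on longer assignment not deterring starting enough to offset the extra days.

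The size is an assumed range. With 10–20% true completion in every arm and independent days, rejection by a nominal 5% test is about 6–7% at q=0.9, 10–16% at q=0.8, 17–35% at q=0.7 and 53–89% at q=0.5. It is about 5–17% if 20–40% never start and the rest are 85–95% adherent. The distortion could therefore be negligible or decisive, and the plan gives no means of telling which.

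**What to change.** Make all randomised participants the primary analysis set for duration and notification level, counting non-beginners as not completed. Alternatively, use one begin criterion with the same opportunity in every arm, such as adherence on day 1. That is a narrower repair, because it still conditions on behaviour after assignment. In either case, keep the present set of beginners as a labelled supportive analysis, report the numbers randomised and begun in each arm, and correct the order of beginning and randomisation in Power and Sample Size.

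No new data are needed: task timestamps and dates of adherence, withdrawal and completion are already recorded. The cost is more than wording. If everyone randomised is analysed, reported completion rates will fall. For either set, the power statement, now 640 beginners at 30/20/10%, must be restated. If those rates hold among beginners, overall duration power for all randomised falls from about 96% to about 89% at q=0.9 or 69% at q=0.7, before the Hsieh correction, so the recruitment target may need to rise.
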